## Abstract

**Introduction:**

Postural orthostatic tachycardia syndrome (POTS) is a multifactorial disorder of the autonomic nervous system characterised by an excessive increase in heart rate (HR) on standing and a wide range of debilitating symptoms, including fatigue, exercise intolerance, cognitive impairment and a high prevalence of depression, anxiety and sleep disturbances. Conventional pharmacological strategies often offer limited relief and do not sufficiently address non-cardiac symptoms. Auricular vagal neuromodulation therapy (AVNT) and slow-paced diaphragmatic breathing (SDB) have each demonstrated promise in modulating autonomic function and alleviating symptom burden but their combined effects in POTS have yet to be investigated.

**Methods and analysis:**

This single-centre, partially blinded, 12-week randomised controlled trial will be conducted at the Medical University of Vienna. A total of 100 participants with confirmed POTS will be recruited, with 25 per group. This sample size is already accounting for an anticipated 30% dropout rate. Participants will be randomised using stratified block randomisation with a 1:1:1:1 allocation ratio, stratified based on the presence or absence of post-exertional malaise (yes/no) to one of four groups: (1) AVNT+SDB, (2) AVNT+normal breathing, (3) sham AVNT+SDB and (4) sham AVNT+normal breathing. The primary endpoint is the change in orthostatic HR (ΔHR) during a 70° head-up tilt test. Secondary outcomes include beat-to-beat blood pressure responses, respiratory sinus arrhythmia, end-tidal CO₂, handgrip strength, activity monitoring and validated patient-reported measures, including Chalder Fatigue Scale, Malmö POTS Symptom Score, Nijmegen Questionnaire, Short Form Health Survey, Hospital Anxiety and Depression Scale and Vanderbilt Orthostatic Symptom Score. Interventions consist of daily 60-minute AVNT (or sham) sessions combined with standardised breathing training (10–15 min/day).

**Ethics and dissemination:**

This study has been approved by the Ethics Committee of the Medical University of Vienna (EK number 1270/2024) and will be conducted in accordance with the Declaration of Helsinki and International Conference on Harmonisation-Good Clinical Practice guidelines. Results will be disseminated through peer-reviewed publications, conference presentations and reporting in the trial registry. Participants will receive study results in an accessible format.

**Trial registration number:**

NCT06996314.

STRENGTHS AND LIMITATIONS OF THIS STUDYThis is, to our knowledge, the first randomised controlled trial to investigate the combined effects of auricular vagal neuromodulation therapy and slow-paced diaphragmatic breathing in postural orthostatic tachycardia syndrome.The 2×2 factorial design allows evaluation of both individual and combined intervention effects. The study includes objective autonomic measurements alongside validated patient-reported outcomes.The single-centre design may limit generalisability of the findings. Blinding is not feasible for the breathing intervention, which may introduce performance bias.

## Introduction

###  Background and rationale

Postural orthostatic tachycardia syndrome (POTS) is a complex disorder of the autonomic nervous system, manifesting as a substantial heart rate (HR) increment of over 30 beats per minute on transitioning to an upright position, without an accompanying decrease in blood pressure (BP).^1^ The underlying pathophysiological theories encompass autoimmune and auto-inflammatory responses,^2^ alongside small fibre peripheral and autonomic neuropathy, hyperadrenergic states and hypovolaemia.^3 4^

POTS can be triggered by biological, psychological and social factors, such as viral infections, vaccinations, pregnancy, surgical procedures, physical trauma and psychosocial stressors.^2 5^ POTS markedly impairs both physical and cognitive abilities, with patients suffering from chronic fatigue, dizziness and exercise intolerance that cause decreased daily activity and worsening deconditioning.^6^ Cognitive symptoms, such as ‘brain fog’, difficulties with concentration and memory issues, arise from autonomic dysfunction and decreased cerebral blood flow.^7 8^ These challenges are intensified by high rates of depression (87%), sleep disturbances (over 50%) and anxiety, forming a complex symptom burden that further worsens the condition.^9 10^ Epidemiologically, POTS affects an estimated 0.2% to 1.0% of the population in developed nations, with a notable predominance among females (with a female to male ratio of 5:1). Challenges in the clinical recognition of POTS often lead to misdiagnoses and delays in accurate diagnosis, highlighting the need for increased awareness and understanding of this condition.^11 12^

While a 2018 systematic review highlighted limited evidence for effective management,^13^ more recent analyses support integrated approaches that combine pharmacological and non-pharmacological strategies.^14^ Traditional pharmacological treatments aim to reduce excessive HR through volume expansion (hydration, sodium supplementation, fludrocortisone), venous pooling reduction (compression garments, midodrine), parasympathetic enhancement (cholinesterase inhibitors), sympathetic modulation (β-blockers, α2-agonists) and direct HR control (ivabradine).^15^ However, these approaches often provide limited relief and are linked to both cardiac and non-cardiac side effects, failing to effectively address non-cardiac symptoms.^16 17^

Although there have been limited studies examining the impact of Auricular Vagal Neuromodulation Therapy (AVNT) on POTS, emerging evidence from case reports and clinical trials indicates its potential.^18 19^ Notably, a recent double-blind, sham-controlled trial study^20^ revealed that daily AVNT for 2 months notably enhances postural tachycardia and autonomic symptoms, indicating improved autonomic control and vascular function without affecting BP. AVNT has also been associated with improved autonomic regulation and reduced inflammatory markers, highlighting its therapeutic potential in POTS. Further research is needed to explore its combination with other treatments and to optimise stimulation parameters. Respiratory-gated AVNT, particularly during the expiratory phase, may further enhance its effects due to physiological variations in vagal activity during breathing.^21^ In addition to AVNT, studies suggest that 80%–90% of POTS patients experience dysfunctional breathing (DB), with up to 65% experiencing severe breathlessness even at rest.^22^ Therefore, the management of DB has emerged as another important aspect of POTS management. DB manifests as a variety of respiratory abnormalities, including hyperventilation, periodic deep sighs, thoracic-dominated breathing, forced abdominal expiration and thoracoabdominal asynchrony.^23^ Although DB is considered a symptom rather than a cause of POTS, its prevalence makes it an important target for intervention. Because breathing, unlike many other autonomic functions, can be consciously perceived and controlled, it offers a unique opportunity for behavioural interventions that target the autonomic nervous system.^24^ Specifically, incorporating slow-paced diaphragmatic breathing (SDB) at 0.1 Hz has been shown to enhance vagal activity.^25^ This suggests that combining slow-paced breathing techniques with AVNT could potentially optimise therapeutic efficacy for POTS patients.

However, despite the individual promise of both AVNT and breathing techniques, their combined effects in POTS have not yet been investigated. To address this gap, we propose a randomised controlled trial (RCT) to evaluate the efficacy and feasibility of an integrated approach combining AVNT with slow-paced breathing. This study aims to explore potential synergistic effects and improve symptom management in patients with POTS. Both interventions have favourable safety profiles; transcutaneous auricular vagus stimulation is generally associated with mild, transient local effects, while SDB may occasionally cause light-headedness if performed incorrectly. These risks will be minimised through standardised instruction and monitoring. A 2×2 factorial design (active vs sham AVNT; SDB vs normal breathing (NB)) was selected to assess both individual and combined effects, while maintaining statistical efficiency. Sham AVNT controls for device-related effects, and normal breathing isolates the specific contribution of slow-paced breathing.

### Objectives

The main aim is to assess whether 12 weeks of AVNT combined with SDB (AVNT+SDB) produces a greater improvement in autonomic function, measured as a reduction in the orthostatic HR change (ΔHR) during a standardised 70° head-up tilt, than AVNT+NB, sham AVNT+SDB or sham AVNT+NB. ΔHR is predefined as the mean HR during the 10-minute upright head-up tilt phase minus the mean HR during the 10-minute supine baseline period; comparisons between AVNT+SDB and each other group are confirmatory, while all other pairwise comparisons are exploratory.

Secondary objectives include characterising between-group differences in beat-to-beat BP responses (mean arterial pressure (ΔMAP), systolic BP (ΔSBP), diastolic BP (ΔDBP), the initial orthostatic nadir, and time to recovery). Respiratory sinus arrhythmia (RSA) is assessed as an index of cardiac vagal modulation using ECG-derived HR variability (HRV), assessing patient-reported outcomes using the Short Form Health Survey (SF-36) for health-related quality of life, the Hospital Anxiety and Depression Scale (HADS) for symptoms of anxiety and depression, Chalder Fatigue Scale (CFS), the Malmö POTS Symptom Score (MAPS) and the Nijmegen Questionnaire (NQ) for symptoms of dysfunctional breathing.

As a safety objective, the trial will evaluate tolerability and systematically record adverse events (AEs) and serious AEs (SAEs), including treatment-related discontinuations, throughout the study, with descriptive comparisons of event profiles across the four groups.

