### Sample size calculation

As no study has yet defined the minimal clinically important difference for HR reduction in POTS, we consider the results of Stavrakis *et al*^20^ to be clinically relevant and have therefore used them as the basis for our sample size calculation. In addition, in the absence of direct clinical data on the effect of slow breathing training on POTS, we assumed an additional reduction from slow breathing training based on studies showing that slow breathing training can reduce HR by approximately 4–10 bpm in various cardiovascular conditions.^34 39 40^ We have used a conservative estimate of seven beats per minute, which we believe to be a minimal clinical difference. This reduction represents not only a measurable physiological change but may also contribute to psychological well-being, as studies suggest.^41^ For our clinical trial investigating the effects of AVNT with and without breathing training and a sham AVNT intervention, we calculated the required sample size based on expected HR changes (ΔHR). This calculation was performed for an analysis of variance using HR data from Stavrakis *et al*^20^ and incorporating an assumed reduction of 7 bpm from slow breathing. Although Stavrakis *et al*^20^ reported no significant reduction in HR in the sham AVNT group, we conservatively assumed a placebo-related reduction of 2 bpm for both sham conditions to account for potential expectancy effects.

We estimated the following mean ΔHR values across the four groups:

AVNT with NB: 17.6 bpm (as reported by Stavrakis *et al*)^20^AVNT with slow-paced breathing: 10.6 bpm (17.6–7 bpm)Sham AVNT with slow-paced breathing: 22.7 bpm (placebo-adjusted 2 bpm reduction from 31.7 and 7 bpm reduction from slow-paced breathing)Sham AVNT with NB: 29.7 bpm (placebo-adjusted 2 bpm reduction from 31.7 bpm)

Assuming an SD of 14 bpm, an alpha level of 0.0167 (Bonferroni correction for 3 pairwise comparisons across four groups), and a power of 80%, 17 participants per group are required for sufficient statistical power. To account for an anticipated 30% dropout rate, 25 participants per group will be recruited, resulting in a total sample size of 100 participants.

Sample size was computed using the University of Vienna’s online analysis of variance (ANOVA) calculator: https://homepage.univie.ac.at/robin.ristl/samplesize.php?test=anova

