### Statistical methods

Statistical analyses will be conducted using IBM SPSS Statistics version 28.0 for Windows (IBM). Continuous variables will be expressed as mean±SD deviation (SD), while categorical variables will be shown as frequencies and percentages with 95% CIs. The primary endpoint, HR change (ΔHR), defined as the difference between upright and supine HR, will be analysed using repeated-measures ANOVA with Bonferroni correction applied to account for multiple comparisons. The main comparison will focus on the change in ΔHR from baseline to week 12 across the four intervention groups. Exploratory secondary analyses will examine changes in BP, HRV, RSA, handgrip strength and patient-reported outcomes (MAPS, CFS, SF-12, HADS). For these outcomes, linear regression models incorporating baseline values, age, sex and medication as covariates will be employed. Interaction terms for time-by-group will be included to identify potential differences in trajectories over time. Assumptions of normality and homoscedasticity will be assessed with QQ-plots and residual plots. When appropriate, non-parametric methods will be used for sensitivity analyses. Analyses will follow the intention-to-treat principle, including all randomised participants according to their allocated intervention group, regardless of adherence or protocol deviations. An additional per-protocol analysis will be performed as a sensitivity check, limited to participants with ≥80% adherence to the intervention protocol. Missing data will be addressed through multiple imputation under the assumption of missing at random. Sensitivity analyses will also be conducted using last observation carried forward and complete-case analysis to evaluate robustness. Regarding the results, study nurses will systematically document reasons for missing data in the case report forms. All confirmatory tests for the primary outcome will be two-sided, with a significance level set at α=0.05, adjusted for multiple comparisons using Bonferroni correction. P values from secondary analyses will be considered exploratory and interpreted accordingly.

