## Discussion

To our knowledge, this protocol represents the first controlled study to investigate the combined effects of AVNT and SDB in patients with POTS, employing a 2×2 factorial design with four treatment arms to assess both main effects and interaction effects between interventions. This research directly addresses a crucial gap in evidence-based, multimodal management of POTS.

The factorial design will assess whether combining vagal neuromodulation with respiratory training yields superior outcomes compared with each intervention individually. AVNT has already demonstrated promise in a sham-controlled, double-blind RCT, where it significantly reduced orthostatic tachycardia and improved autonomic markers compared with sham stimulation over a 2-month period 21. Similarly, even brief slow deep abdominal breathing at six breaths/min has been shown to significantly reduce standing HR and improve symptom scores in POTS patients during tilt testing.^34^ If additive or synergistic effects are observed, this combined approach may offer a scalable, patient-autonomous and low-risk therapeutic strategy.

Our trial combines objective measures such as HRV, BP responses and validated patient-reported outcomes, providing a comprehensive and multidimensional assessment. The inclusion of a sound-sham AVNT control reduces expectancy bias, while the 12-week intervention period balances therapeutic exposure with practicality for this vulnerable population. Beyond its clinical relevance, this study establishes the groundwork for multimodal autonomic therapy in POTS. The factorial design enables the identification of responder profiles and supports the development of stratified treatment approaches, pushing the field towards precision medicine in autonomic disorders.

Should the combined intervention demonstrate superior efficacy, findings will inform clinical guidelines and healthcare policy regarding non-pharmacological POTS interventions. The ability to deliver both therapies through structured patient training offers potential for scalable, cost-effective treatment that enhances patient autonomy while reducing long-term healthcare burden.

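### No rule says which of the three confirmatory comparisons support the claim that the combination beats each component, and Bonferroni gives up power that Holm keeps at the same familywise error

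*Protocol article*

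**What the plan says.** The Objectives of the protocol article set one main aim: that AVNT+SDB lowers ΔHR more "than AVNT+NB, sham AVNT+SDB or sham AVNT+NB". They then fix the confirmatory family: "comparisons between AVNT+SDB and each other group are confirmatory, while all other pairwise comparisons are exploratory".

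The Sample size calculation uses "an alpha level of 0.0167 (Bonferroni correction for 3 pairwise comparisons across four groups"). Statistical methods repeats the adjustment: "All confirmatory tests for the primary outcome will be two-sided, with a significance level set at α=0.05, adjusted for multiple comparisons using Bonferroni correction". The same section describes the primary contrast differently: "The main comparison will focus on the change in ΔHR from baseline to week 12 across the four intervention groups".

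The Discussion states the question that the factorial design is meant to answer: "whether combining vagal neuromodulation with respiratory training yields superior outcomes compared with each intervention individually". It adds that superior efficacy of the combined intervention would inform guidelines and health policy.

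No section says how many of the three comparisons must be significant, in what order they are tested, or which result supports which conclusion.

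**The concern.** The three comparisons answer different questions. AVNT+SDB against AVNT+NB asks whether slow breathing adds to AVNT. AVNT+SDB against sham AVNT+SDB asks whether AVNT adds to slow breathing. AVNT+SDB against sham AVNT+NB asks only whether the package beats double control, and it can be won when just one component works. Superiority to each intervention individually needs the first two together.

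The protocol fixes the aim, the family and the alpha split but does not tie them to that claim. A Bonferroni split protects a claim of at least one difference, and the aim joins the comparators with *or*. A reader could therefore take any single win as meeting the main aim. The easiest comparison is the least informative about combining, so the choice of reading matters a great deal. If it is made after the results are known, it will not be credible.

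A second, smaller matter is the adjustment itself. Bonferroni over three tests is valid, but Holm has the same familywise error and rejects everything that Bonferroni rejects, sometimes more. Here the gain falls on the two comparisons that bear on the combination.

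**Working it through.** **Inputs (Sample size calculation).** Mean ΔHR: AVNT+SDB 10.6, AVNT+NB 17.6, sham AVNT+SDB 22.7, sham AVNT+NB 29.7 bpm. SD 14. Alpha 0.0167. 17 per group, 25 after 30% dropout.

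**1. The plan's own figure.** One-way ANOVA F test, noncentrality λ = n·Σ(μᵢ − μ̄)²/σ². The grand mean is 80.6/4 = 20.15. The sum of squares is 2 × (9.55² + 2.55²) = 195.41. At n = 17, λ = 17 × 195.41/196 = 16.95, giving power 85.1%. The smallest n reaching 80% is 16 (82.0%), so the stated 17 is reproduced within one patient per group. Dropout: 17/0.70 = 24.3, rounded up to 25. This is power for the overall F test, not for any of the three confirmatory comparisons.

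**2. Power for each confirmatory comparison, n = 17.** Standard error 14·√(2/17) = 4.80. Two-sided critical value at 0.05/3 on 64 df: 2.459.

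| AVNT+SDB against | Difference (bpm) | Noncentrality | Power |
|---|---|---|---|
| AVNT+NB | 7.0 | 7.0/4.80 = 1.46 | 17% |
| sham AVNT+SDB | 12.1 | 12.1/4.80 = 2.52 | 53% |
| sham AVNT+NB | 19.1 | 19.1/4.80 = 3.98 | 93% |

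**3. Joint results.** The three tests share the AVNT+SDB arm, so they are correlated and were simulated together (400,000 trials, pooled variance, two-sided 0.05/3, favourable wins counted), n = 17:
- at least one win: 94%
- both component comparisons won: 14%
- at least one win but not both components: 80%
- double sham as the only win: 39%

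**4. If slow breathing adds nothing.** Means 17.6, 17.6, 29.7, 29.7 in the same order of arms. At 17 per group:
- win over AVNT+NB: 0.8%
- win over sham AVNT+SDB: 53%
- win over sham AVNT+NB: 53%
- at least one win: 69% (86% at 25 per group)
- both components: 0.8%
- double sham as the only win: 16% (13% at 25 per group)

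**5. Holm in place of Bonferroni.** Order the three p values and compare them in turn with 0.05/3, 0.05/2 and 0.05, stopping at the first failure. Planned means:

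| | Bonferroni, n = 17 | Holm, n = 17 | Bonferroni, n = 25 | Holm, n = 25 |
|---|---|---|---|---|
| vs AVNT+NB | 17% | 28% | 26% | 40% |
| vs sham AVNT+SDB | 53% | 60% | 73% | 79% |
| both components | 14% | 26% | 24% | 39% |

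No simulated trial lost a rejection by moving to Holm. With all four means equal, the two-sided chance of any rejection was 4.4% under either method. If slow breathing adds nothing, Holm with a both-components rule gives a wrong combination claim in 2.3% of trials at 17 per group.

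**The case against.** A reader might infer that the main aim can be declared met by beating double sham alone, or that the plan carries a 69% false-positive rate. The documents support neither.

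- The protocol nowhere says that one win suffices. *Better than A, B or C* can mean better than each, and the same paragraph refers to each other group. The Discussion names the right comparators for the combination claim. Bonferroni is also a normal adjustment for three separate claims, so it does not by itself establish an any-one-wins rule.
- The 69% is not an error rate. In that scenario AVNT+SDB truly is better than both sham arms, so those rejections are correct. The error that matters, a win over AVNT+NB when slow breathing is inert, occurs in 0.8% of trials.
- Double sham is not the only route to an uninformative win. With inert breathing, sham AVNT+SDB is beaten just as often (53%), and double sham is the sole win in only 16%.

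All of this stands, and it limits the point to an unstated link between tests and claim.

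It can also be said that an analysis plan, not shown, may hold the rule. But the article itself fixes the aim, the family and the alpha, and states the claim; the link between them belongs in the same place.

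Finally, Bonferroni is valid, and a both-must-win claim needs no alpha split at all: at 0.05 per test its joint power is about 27% at 17 per group. True, but Holm reaches nearly the same (26%) while still protecting each of the three comparisons as a separate claim.

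**Conclusion.** The point holds as a gap in the decision rule and a better choice of adjustment, not as a failure of type I error control. As written, the chance of at least one significant confirmatory comparison (94%) and the chance of the results that would support superiority to each component (14%) differ by 80 percentage points, and the protocol does not say which of the two counts. Holm narrows the gap but does not close it: 26% at 17 per group, 39% if all 25 per group are analysed.

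The figures rest on the plan's own means, a common SD of 14, normal data, 17 or 25 analysed per group, and pooled-variance tests of follow-up ΔHR, as in the sample size section. The protocol gives no baseline correlation, so any gain from using baseline is not counted.

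**What to change.** 1. In Statistical methods, replace Bonferroni by Holm over the three confirmatory comparisons, familywise 0.05 two-sided. Cost: confidence intervals that match Holm decisions are less simple than Bonferroni intervals.

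2. In Objectives and Statistical methods, state that superiority of the combination to each component is claimed only if AVNT+SDB is significantly better than both AVNT+NB and sham AVNT+SDB, and that a win over sham AVNT+NB alone supports only better than double control.

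3. In the Sample size calculation, state the joint power for the combination claim on the planning assumptions: about 26% at 17 per group with Holm, 39% at 25. This is the real cost, because a positive combination claim is unlikely at the planned size. An 80% joint power would need about 63 analysed per group at 0.05 per test (63/0.70 = 90 recruited per group, 360 in total, against 100 planned). Enlargement is not proposed; the figure should simply be disclosed.

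Enrolment began on 19 March 2026 and no interim analysis is planned, so the change can go through the stated amendment route before outcome data are compared by arm.
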